### Data collection, cleaning and storage

In the intervention states, the children enrolled in the study will be managed according to the state specific CSAM guidelines and locally produced nutrient dense food supplements. The study will assess the effectiveness of the CSAM programmes in terms of recovery of these children compared to the comparison arm. This will be assessed using anthropometric (length/height and weight) measurements and skinfold thickness (triceps and sub-scapular) to be taken on admission, at sixth week and at discharge by the trained field investigator. For anthropometric measurements, a digital weighing machine with a sensitivity of 10 g to measure weight and a wooden infant-cum-stadiometer to measure length/ height will be used. Length and height will be measured to the nearest 0.1 cm, weight to the nearest 0.01 kg and skinfold thickness to the nearest 0.1 cm. Weighing equipment will be calibrated using standard calibration weights and infant-cum-stadiometer will be calibrated with calibration rods. The skinfold caliper will also be calibrated daily. Before doing the data collection work, all Field Investigators will be trained and also complete anthropometric standardization exercises where their anthropometric measurement skills will be assessed for thoroughness, accuracy and precision. To assess the accuracy and precision of each Field Investigator, their measures will be compared to those of the master trainers, who will be considered the gold standard. Intra-observer technical error of measurement (TEM) and reliability will be calculated using the difference between the two measures of the Field Investigators. Inter-observer TEM and reliability will be calculated by comparing the Field Investigators two measures to the trainer’s measure [27].

Also, during admission and at discharge, the Field Investigator will administer the questionnaire for capturing child details and incidences of morbidity. Additionally, during admission, data on availability of drinking and sanitation facilities and other household level socio-economic information will be collected. Also,24-h dietary recall, food frequency and food consumption questionnaires will be administered to these children on admission, at sixth week and at discharge to study food consumed by the children, food frequency and compliance of locally produced nutrient dense food supplements provided to the children as part of the intervention. Futhermore, we will also ascertain cause of death of any enrolled child died during the study period.

Besides, first 100 enrolled children in that state who qualifies for body composition measurement i.e. weight on admission > 5 kg, will also be measured for body composition parameters using BIA machine (InBody S10) on admission and at discharge.

Post discharge, the children will be followed up on a monthly basis for anthropometry until 6 months by the field investigators. Additionally, skinfold thickness and body composition assessment of all children will also be repeated at sixth month post discharge. A detailed description of data collection process is shown in Table 2.

**Table 2 Tab2:** Overview of all measurements that will be taken from children

Parameters	Method	Admission/ Baseline	6th Week	12th/16thweek/Exit/Discharge	Post-discharge Follow up^b^
All children enrolled:					
Child details, and history of illness	Questionnaire	**✓**		**✓**	
Drinking water and sanitation facilities and other household socio-economic status		**✓**			
Weight, Recumbent length/ Height,	Digital weighing machine, Infantometer/ Stadiometer	**✓**	**✓**	**✓**	✓
Skinfold Thickness (triceps & subscapular skinfold)	Holtain Skinfold Caliper	**✓**	**✓**	**✓**	✓^c^
Dietary assessment (24-h dietary recall & food frequency) and Consumption of locally produced nutrient dense food	Observation and questionnaire	**✓**^**a**^	**✓**	**✓**	
Body composition; For enrolled sub-sample of children (weight > 5 kg)					
Body fat mass	BIA machine	✓		✓	
Body lean mass					✓^c^

^a^At baseline only the 24-h dietary recall & food frequency assessment will be done

^b^Post discharge, all children will be prospectively followed up for anthropometric measurements on a monthly basis till 6 months by the field investigators

^c^Additionally, skinfold thickness and body composition assessment of all children will also be repeated at 6^th^ month post discharge

We will use mobile phones programmed using the Kobocollect platform for data collection. Every child will be given a unique number which will be used to link the database of the child to be collected at different time points. The monitoring team will check the number of interviews completed and type of data collected on regular basis in order to promptly identify and address possible problems. The data will be downloaded regularly and checked for errors using automated do files and manual inspections. The data will be stored and backed up every 2 weeks on a server.

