**Methods:**

The longitudinal quasi-experimental study will be undertaken in two purposively selected blocks of one district each in the four intervention states and one comparison state. From each state, 200 SAM children identified using weight-for-length/height z-score (WHZ) < **−** 3 criteria will be enrolled in the study. Their anthropometric data and skinfold thickness will be taken on admission, at sixth week and at discharge by trained field investigators. Other child details, incidence of morbidity and socio-economic details will be collected on admission. To assess food consumption pattern including consumption of locally produced nutrient dense food supplements, dietary assessment, using 24-**h** dietary recall will be conducted on admission, at sixth week and at discharge. In addition, body composition parameters will be assessed for a sub-set of children using bio-electrical impedance analysis on admission and at discharge to analyse changes in total body water, fat-free mass, and fat mass. Post discharge, all study participants will be followed up monthly until 6 months. Atleast 10% of the sample will be checked for quality assessment.

The study’s primary outcome is cure rate defined as children attaining WHZ **≥** -2. Secondary outcomes include mean weight gain, mean length of stay, body composition parameters, relapse and mortality rates. Additionally, process evaluation and cost effectiveness analysis will be conducted.

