### Intervention strategy

In general, the State Governments of Telangana, Madhya Pradesh, Odisha and Chhattisgarh will implement community-based management of SAM (CSAM) programme adapted from the WHO guidelines, in addition to the existing government nutrition promotion interventions. The approach will incorporate active and/or passive case-finding and screening for severe wasting by government frontline nutrition and health workers. For uniformity, children with WHZ < -3 will be categorized as experiencing SAM. SAM children will further undergo medical examinations and appetite test to identify complicated and uncomplicated cases. All complicated cases will be referred to the nearest nutritional rehabilitation centres (NRCs) for in-patient management. All uncomplicated cases will be enrolled in the CSAM programme for their community-based management in *anganwadi centres*. While the program’s primary focus is on treatment of children who are severely wasted, key activities also include regular follow up of all enrolled children at the *anganwadi centers*, counseling of caregivers on infant and young child feeding (IYCF), safe water, sanitation and hygiene practices, family planning and child care practices, promotion of vaccinations, appropriate referrals of sick children to NRCs or public health facilities and post discharge follow up. SAM children enrolled in the programme will also be given locally produced nutrient dense food supplements, antibiotics, anthelminthic and micronutrient supplements. Key aspects of the state specific CSAM programme are presented in Table 1. Detailed description of the state specific CSAM protocols and nutritional content of each locally produced nutrient dense food supplement is provided in Additional file 1. In the comparison area, where no CSAM intervention is being implemented, SAM children identified and enrolled in the study will receive the existing government nutrition promotion interventions. The existing program includes provision of double quantity of Take Home Ration (THR)^1^ for severely underweight children (which covers most of SAM children) and identification and referral of SAM children to Malnutrition Treatment Centres (MTCs).

**Table 1 Tab1:** Key aspects of the CSAM protocol that vary per state assessed

States	Screening & Identification	Admission criteria	Maximum treatment duration	Discharge criteria	Nutrient dense food	Post-discharge Follow up

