### Sample size

The primary outcome of the study is cure rate at 12 weeks (in Chhattisgarh) or 16 weeks (in Telangana, Madhya Pradesh and Odisha) compared to the comparison area. Evidence on CMAM interventions in India testing its efficacy have shown cure rates ranging from 46.7 to 57.4% [19–23]. Another study from India found cure rate among 25–30% children with minimal community based interventions [26]. Hence for the sample size calculation, we therefore chose the expected cure rate with the proposed CSAM interventions of 50% and expected cure rate with existing government nutritional interventions of 25% to estimate the effect size of 25% (50–25%). The sample in each state will comprise of an equal proportion of children from the two age groups (6–23 months and 24–59 months). Using the significance level of 5%, with 80% power to detect the effect size of 25%, a design effect of 1.5 and accounting for 20% attrition due to loss of follow up and mortality, the sample size calculated for each age group of children is 100. Hence, the proposed sample size for the two age-groups of children in each state is 200 children. In total, the study will enroll 1000 children in all the five study states.

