### Data analysis

Final analysis will include all children enrolled in the study. Appropriate quantitative analyses will be used including descriptive statistics (proportion, percentage, mean or median), comparison of difference in proportion for binary outcome using Pearson chi-square and comparison of average change for continuous variable using t-tests. Recovery will be compared for effectiveness of state specific CSAM protocols and locally produced nutrient dense food supplements in four intervention states in comparison to the comparison state. Cox regression method will also be used for this analysis by defining recovery as event, as it can utilize the entire sample size including defaulters or loss to follow up. Other parameters including skinfold, defaulting, death, length of stay, average weekly weight gain and height gain will also be compared between the intervention states and the control state. Subgroup analysis will be done for comparing recovery among children aged 6–23 months and 24–59 months between intervention states and control state. For the sub-sample of body composition, change in fat mass, fat free mass and body water will be compared between the four intervention states and the comparison state. A linear mixed model will be developed for different outcomes (recovery, weight gain, and body composition parameters) adjusting for various random and fixed effects across all sites adjusted for differences at baseline.

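### The final recovery reading is tied to programme discharge, which the cure threshold itself triggers in the CSAM states and which is undefined in the comparison state

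*Protocol article*

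**What the plan says.** - **Outcome.** The abstract's Methods paragraph says the "primary outcome is cure rate defined as children attaining WHZ" of −2 or above. The Sample size section adds timing, with the untreated area as reference: "The primary outcome of the study is cure rate at 12 weeks (in Chhattisgarh) or 16 weeks (in Telangana, Madhya Pradesh and Odisha) compared to". It gives no week for the comparison area itself.
- **Visits.** Under Data collection, cleaning and storage, the length/height, weight and skinfold readings used to judge recovery are "to be taken on admission, at sixth week and at discharge by the trained field investigator". Table 2 heads the last in-treatment visit "12th/16thweek/Exit/Discharge", for all enrolled children. After discharge, field investigators take anthropometry monthly for six months.
- **Discharge.** Table 1 ("Key aspects of the CSAM protocol that vary per state assessed") gives all four CSAM states the same discharge criterion, WHZ of −2 or above, with a maximum treatment duration. It has no row for the comparison state. The Intervention strategy section says: "In the comparison area, where no CSAM intervention is being implemented", enrolled children receive the existing services.
- **Analysis.** The Data analysis section includes all enrolled children, compares proportions by Pearson chi-square, and adds a Cox model with recovery as the event, "as it can utilize the entire sample size including defaulters or loss to follow up". It also plans further contrasts of CSAM states with the control state: "Other parameters including skinfold, defaulting, death, length of stay, average weekly weight gain and height gain will also be compared".

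**The concern.** In the CSAM states the event that ends treatment is the same event that counts as cure. If the final reading is taken at discharge, its timing depends on the outcome: a child who touches −2 early is measured then and recorded as cured. A comparison child has no such trigger, and the article does not say when that child's final reading falls. The natural inference from Table 2 is a set week.

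A first crossing looked for on several occasions gives a higher proportion than status on one set occasion, even when growth is identical. The same asymmetry reaches three other analyses:

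- **Cox model.** Recovery can be dated at any discharge in a CSAM state, but only at week 6 or an unspecified final visit in the comparison state.
- **Weight gain and body-composition change.** The interval can end at success in the CSAM states only.
- **Length of stay and defaulting.** Neither has a meaning where there is no programme.

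The primary contrast is at stake. A reading that was never scheduled cannot be recovered by later analysis.

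**Working it through.** **1. The passages side by side.**

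| Item | CSAM states | Comparison state |
|---|---|---|
| Week of the primary outcome (Sample size) | 12 or 16 | none given |
| Discharge rule (Table 1) | WHZ ≥ −2, or maximum duration | none given |
| Final reading (Data collection; Table 2) | week 12/16, exit or discharge | same column, but no exit or discharge exists |

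A child discharged at week 7 has no scheduled reading at week 12 or 16, because the monthly follow-up is counted from discharge and not from enrolment. The week itself is also unsettled. The Sample size section gives Chhattisgarh 12 weeks and Madhya Pradesh 16, while Table 1 gives them 16 and 12.

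**2. The plan's own figure.** Inputs from the Sample size section: cure 50% v 25%, 5% significance (two-sided assumed), 80% power, design effect 1.5, attrition 20%.

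n = (1.960 + 0.842)² × [0.5×0.5 + 0.25×0.75] / 0.25² = 7.849 × 0.4375 / 0.0625 = 54.9, so 55.

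55 × 1.5 × 1.2 = 99, which matches the stated 100 per age group. The sample size is not in dispute. The effective number per state is 200 × 0.8 / 1.5 = 106.7.

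**3. Size of the artefact with identical arms.** All inputs here are assumptions, since the article gives neither contact frequency nor WHZ variability. Baseline WHZ is −3 − |N(0, 0.4)|. Gain is linear with between-child SD 0.6, its mean set so that 25% are at or above −2 at the final visit. Weekly fluctuation is autoregressive (correlation 0.8), with measurement error added. The three entries per cell use fluctuation/measurement SDs of 0.1/0.1, 0.2/0.15 and 0.3/0.2. The gap is the share at or above −2 at any contact minus the share at the final visit, in percentage points.

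| Horizon | Weekly contacts | Fortnightly | Four-weekly |
|---|---|---|---|
| 12 weeks | 1.3 / 4.1 / 8.3 | 0.4 / 1.8 / 4.4 | 0.0 / 0.5 / 1.8 |
| 16 weeks | 2.0 / 5.7 / 11.0 | 0.8 / 3.0 / 6.8 | 0.1 / 1.1 / 3.2 |

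At 106.7 effective children per state, the chance of a false finding for CSAM runs from 2.5% (the nominal upper tail) to 41%. With four-weekly contacts it is at most 7.6%. Crediting comparison children for week 6 as well raises their rate by only 0 to 0.7 point. If both arms are scored by one rule on the same visits, the artefact is zero by construction.

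**4. Effect of the scoring rule on power.** Suppose the planned 50% is an ever-attained rate, and a share r of those children (assumed) are below −2 again at the fixed week. The fixed-week rate is 0.50 × (1 − r): 45%, 40% and 35% for r = 10%, 20% and 30%. Power against 25% at 106.7 per state falls from 97% to 87%, 65% and 36%.

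**5. Not quantified.** For the Cox model, weight gain and body composition I give direction only. A comparison child who crosses between visits is dated later than a CSAM child with the same growth. An interval that stops at a crossing tends to stop on an upward fluctuation.

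**The case against.** The strongest reply is that the Sample size section does fix the primary outcome at 12 or 16 weeks, and that Table 2 applies one visit to all enrolled children. On that reading every child has a fixed-week result. This carries weight: a reader might infer two established scoring rules, ever reaching −2 for CSAM children and status at one visit for comparison children, and the article states neither. It gives no contact frequency (state protocols are in an additional file not shown). It does not say whether a worker's finding at discharge must be confirmed by the field investigator's reading, which would shrink a noise-driven gap and is not in the simulation. What remains is that the Sample size section, the data collection text and Table 2 are not reconciled, and that the comparison child's final visit is undefined.

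A reader might also infer that defaulters are dropped from the cure rate or that deaths do not count as failures. Neither is supported. The final analysis includes all enrolled children. Censoring of defaulters is implied only for the Cox model, where losses in the comparison state enter too. The handling of deaths is not stated and can be left to the analysis plan, as can competing-risk, interval-censored or imputation methods.

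Finally, cure is defined as attaining −2, with relapse a separate outcome, so a switch to fixed-week status is not the only remedy. That point stands.

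**Conclusion.** The concern holds as a defect of ascertainment. The final reading is tied to an event that the outcome triggers in four states and that does not exist in the fifth, and the stated 12/16-week horizon neither covers the comparison state nor agrees with Table 1. The bias tends to favour CSAM. Under the assumptions shown, its size is about 0 to 11 points of cure, and about 0 to 3 points with four-weekly checks, against a planned difference of 25 points.

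It would go too far to say that the plan must show CSAM as better when nothing differs. It can do so, and the upper figures need weekly contacts and the highest assumed variability. The comparison of length of stay and defaulting with the control state is wrong whatever those assumptions are. Because the defect concerns the primary contrast and the visit schedule, it should be settled while the study is recruiting.

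**What to change.** 1. State one outcome week, counted from enrolment, for all five states. Field investigators measure every enrolled child then, including those discharged, defaulted or referred, by aligning one of the study's monthly visits. This changes no state's treatment duration.
2. Score cure by one rule on the same study visits in every state: either status at that week, or attained by that week on the common visits. The second stays closer to the present definition; the first may cost power, as in step 4 of the working. Date recovery in the Cox model from those visits.
3. Compare weight gain and body composition over the same fixed interval.
4. Report length of stay and default for the CSAM states only.
5. Reconcile the 12- and 16-week assignments of Madhya Pradesh and Chhattisgarh between Table 1 and the Sample size section. Which is right is not judged here.

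The cost is rewording plus one realigned visit per early-discharged child. The monthly visits carry anthropometry only, with skinfold and body composition repeated at month six, so item 3 also needs those readings at the aligned visit. Study cure rates may come out slightly below programme-reported ones.

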#### Secondary research questions

Do state specific CSAM programmes help recovery of a SAM child, as defined by body composition parameters such as fat mass by skinfold thickness and fat free mass, body water by BIA, in each of the four intervention states?What is the relationship between anthropometry and body composition measures in a child suffering from SAM, in each of the five states?Do state specific CSAM programme provide better outcomes in terms of recovery, defaulting, death, length of stay and average weekly weight gain, compared to existing evidence from India?Which of the CSAM programme provides best rate of recovery 6 months after exit from the programme, defined by the relapse and mortality rates?

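### The stated skinfold recording unit of 0.1 cm (1 mm) adds avoidable noise to a secondary change outcome and may be a cm-for-mm slip

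*Protocol article*

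**What the plan says.** Under *Data collection, cleaning and storage*, one sentence sets the recording precision of all body measurements. It says "Length and height will be measured to the nearest 0.1 cm", gives a precision for weight, and then sets "skinfold thickness to the nearest 0.1 cm". Table 2 names the instrument, a "Holtain Skinfold Caliper", but not its graduation. The caliper is to be calibrated every day, and observers are standardised before fieldwork: "Intra-observer technical error of measurement (TEM) and reliability will be calculated using the difference between the two measures".

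The plan is for "skinfold thickness (triceps and sub-scapular) to be taken on admission, at sixth week and at discharge", and again six months after discharge. The secondary research questions include recovery in terms of "fat mass by skinfold thickness and fat free mass". *Data analysis* lists skinfold among the outcomes compared between intervention and control states ("Other parameters including skinfold, defaulting, death, length of stay"), and continuous outcomes are handled by "comparison of average change for continuous variable using t-tests".

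**The concern.** A unit that suits length or height is coarse for skinfold. If the rule is followed, each triceps and subscapular reading becomes a whole number of millimetres. A reading can then be off by up to 0.5 mm and a child's change by up to 1 mm.

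This sits oddly beside a dedicated caliper, daily calibration and a formal estimate of technical error of measurement (TEM). Skinfold is planned for every enrolled child, whereas bio-electrical impedance on admission and at discharge covers only the first 100 eligible children per state, so for the remaining children skinfold is the planned measure of fatness over treatment. At stake are the precision of the between-state comparison of skinfold change, the quality of the TEM exercise, and the secondary question on how anthropometry relates to body composition.

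**Working it through.** **Inputs from the article.** Recording unit g = 0.1 cm = 1 mm. Planned sample 200 per state, design effect 1.5 and attrition 20% (*Sample size*). The last two are stated for the cure rate and are borrowed here for illustration.

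**Not in the article.** The SD of skinfold change, the expected change and the caliper's graduation. The SD of change is therefore an assumption, varied below. A 0.2 mm unit serves only as an example of a finer one.

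**Rounding error.** Rounding to a grid of width g adds variance g²/12 to a reading and 2 × g²/12 = g²/6 to a change between two visits.
- g = 1 mm: 1/12 = 0.083 mm² per reading (SD 0.29 mm) and 1/6 = 0.167 mm² per change (SD 0.41 mm).
- g = 0.2 mm: 0.04/6 = 0.0067 mm² per change (SD 0.08 mm).

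**Effect on the change score.** Variance inflation is (g²/6)/SD². The equivalent loss of sample is 1 − 1/(1 + inflation). The squared correlation of recorded with true change is SD²/(SD² + g²/6).

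| Assumed SD of change (mm) | Inflation, 1 mm unit | Equivalent loss of sample | Squared correlation | Inflation, 0.2 mm unit |
|---|---|---|---|---|
| 0.8 | 0.167/0.64 = 26% | 21% | 0.79 | 1.0% |
| 1.0 | 0.167/1.00 = 17% | 14% | 0.86 | 0.7% |
| 1.6 | 0.167/2.56 = 7% | 6% | 0.94 | 0.3% |
| 2.0 | 0.167/4.00 = 4% | 4% | 0.96 | 0.2% |

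**Bias.** In a simulation of 400,000 children (assumed baseline 6 mm, SD 1.2 mm), with true mean changes of 0.5, 1, 1.5 and 2 mm and SDs of change from 0.5 to 2 mm, the mean recorded to 1 mm agreed with the mean recorded to a fine unit within 0.005 mm. The mean change is not distorted. Individual records are: with a true mean change of 0.5 mm, 19% (SD 2 mm) to 46% (SD 0.5 mm) of children would be recorded as having exactly no change.

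**Power.** The effective number per state is 200 × 0.8/1.5 = 107. Take the between-state difference that has 80% power with a 0.2 mm unit. With a 1 mm unit, power for the same difference is 70%, 74%, 77% and 78% at SDs of 0.75, 1, 1.5 and 2 mm. At an SD of 0.5 mm it falls to 59%.

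**TEM.** TEM² is half the mean squared difference between paired readings. Rounding adds 2/12 mm² to the variance of a difference, hence 1/12 mm² to TEM², equivalent to 0.29 mm. This holds when true differences are not small against the grid. When they are small, two readings less than 1 mm apart are recorded either as identical or as a full 1 mm apart.

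**Individual relationships.** A correlation between skinfold change and another measure shrinks by the square root of the squared correlation above: by about 11% at SD 0.8 mm (√0.79 = 0.89) and 2% at SD 2.0 mm (√0.96 = 0.98).

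**The case against.** The strongest reply is that this may be no more than a misprint. The same sentence uses 0.1 cm for length and height, and a slip of cm for mm is plausible. The article condenses a fuller protocol, and neither the measurement manual nor the data-capture form is shown. If readings are in fact taken to 0.1 mm, the precision loss falls away and only the text needs correcting. That stands: the documents show the written rule, not what the form does.

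The size is also unanchored. No SD of change is given, and any observed SD will contain observer error, which enlarges it and reduces the relative cost of rounding. At 1 to 2 mm the loss is 4% to 17% of variance and about 2 to 6 points of power. That stands too, and the larger figures should not be taken as the expected ones.

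A reader might infer that the rule throws away much of the change the study wants to detect. The documents do not support that. The planned analysis compares mean change, which rounding leaves essentially unbiased; what is lost is precision. Nor can the whole-millimetre unit be called unsuited to this caliper as a matter of record, because the caliper's graduation is not stated.

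**Conclusion.** The point holds as a minor one. The article states a 1 mm recording unit for an outcome whose change is to be compared between states, and gives no finer unit elsewhere. If followed, the rule adds 0.167 mm² to the variance of each change score: about 4% to 26% inflation over assumed SDs of 2.0 down to 0.8 mm. The cost is material only towards the lower end of that range or below it. The result rests on the rounding model, on the assumed SDs, and on the rule being applied as written.

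The effect is confined to secondary outcomes and the observer-reliability check. The primary outcome, cure by weight-for-height z-score, does not use skinfold.

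**What to change.** Check the caliper's graduation and the precision at which the form actually accepts skinfold. Then state skinfold in millimetres at that graduation, in its own clause apart from length and height, and set the form to match. If the form is already finer than 1 mm, correct the text only.

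The cost is one line of protocol and at most one form field. There is a small downside, because *Trial timeline and status* says recruitment is under way. If whole-millimetre readings have already been taken, date the change and flag them. Their precision cannot be recovered, and a child with a coarse admission reading and a finer discharge reading keeps the admission half of the rounding variance. With a 0.2 mm unit at discharge, for example, the added variance is 1/12 + 0.04/12 = 0.087 mm² instead of 0.167 mm². An early check limits how many children are affected.
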